## Abstract

**Background:**

The assessment of restored teeth in dentistry remains a challenge, mainly related to the detection of caries around restorations. There is a diversity of clinical criteria available to assess the caries lesions, resulting in differences in the dentists’ diagnosis and treatment decisions. In addition, there is a lack of evidence regarding the best criteria to detect caries lesions around the restorations. Thus, the present protocol aims to evaluate the effect of using 2 visual criteria to assess restored teeth on the outcomes related to oral health in adults.

**Methods:**

The design protocol of the Caries Cognition and Identification in Adults trial correspond to a triple-blind randomized, controlled clinical trial with parallel-groups. Two groups will be compared: patients who will receive the diagnosis and treatment decision according to FDI (World Dental Federation) criteria—FDI group; and patients who will receive diagnosis and treatment decision according to the “Caries Associated with Restorations or Sealants” criteria defined by the International Caries Classification and Management System (ICCMS group). The participants will be followed up after 6, 12, 18, 24, and 60 months, and the restoration failure will be the primary outcome. The analysis will be conducted through Cox regression with shared frailty. The impact of oral health on quality of life and the cost-effectiveness of the methods used will be the secondary outcomes. Two-tailed analyzes will be used, considering a level of significance of 5%.

**Discussion:**

This is the first clinical trial to assess the effect of using two visual methods to detect caries lesions around restorations on the outcomes related to oral health in adults. The findings of this study will define what is the best diagnostic strategy for the assessment of caries around restorations in permanent teeth.

*Trial registration* NCT03108586 (registered 11 April 2017).

## Background

Secondary caries was recognized as one of the conditions on dentistry of the highest potential for improving future restorative treatment over the next 20 years [1]. Secondary caries is the designation given to a caries lesion adjacent to a restoration [2]. The scientific literature reports this condition as the main reason for restorations failures [2–5]. A recent review reported that the replacement of failed restorations due to secondary caries represents a high number of the restorations placed by the dentists (28.5–59% of cases). In contrast, the number of failed restorations due to secondary caries is notedly lower (2–3%) in controlled clinical trials [3, 4], which raises doubts about the real prevalence of this condition and the possibility of overtreatment. Besides, the dentists show heterogeneity in the treatment decision-making regarding secondary caries [6, 7].

The correct diagnosis of caries around the restorations is often a challenge for dentists due to aspects as the presence of gaps between the restoration and tooth surface, marginal staining, and due to the development on challenging areas of assessment, such as interproximal areas [8]. Some of these aspects can lead to an erroneous detection of caries lesion [9, 10]. Different clinical criteria have been used in the visual detection of caries around restorations [11], which may imply different interpretations about what is a secondary caries lesion. Among these criteria, two are highlighted due to the current use in research and clinic: the International Dental Federation (FDI) criteria [12] and Caries Associated with Restorations or Sealants (CARS) criteria, described in the International Caries Classification and Management System (ICCMS) [13].

Nevertheless, all studies on methods for caries detection around restorations are cross-sectional accuracy studies [11, 14]. Moreover, most studies fail to present clinical relevance and report patient-centered outcomes [11]. No randomized clinical trial has been conducted to test the best method to detect caries around restorations. Thus, we will run a randomized clinical trial to investigate the best approach to the diagnosis and decision of treatment of restorations in adults. The present protocol will aim to evaluate the effect of using 2 visual criteria, FDI and CARS criteria to assess restored teeth on the outcomes related to oral health in adults.

## Methods

### Trial design

This is a triple-blind randomized, controlled, parallel-group clinical trial. Two groups will be compared: patients who will receive the diagnosis and treatment decision according to FDI criteria [12]—FDI group; and patients who will receive diagnosis and treatment decision according to the “Caries Associated with Restorations or Sealants” (CARS) criteria from ICCMS [13]—ICCMS group. The trial—Caries Cognition and Identification in Adults (CaCIA) trial—has been registered with ClinicalTrial.gov (NCT03108586) and is currently in the active phase. The Standard Protocol Items for Clinical Trials (SPIRIT) were used to guide the present protocol as detailed in the Additional file 1: Appendix (appendix 1).

### Participants, interventions, and outcomes

#### Setting

The study will be conducted at the clinic at the School of Dentistry of the Federal University of Pelotas (UFPel). The patients (18 to 60 years old) will be randomly selected from a list of patients seeking dental treatment at the School of Dentistry.

#### Eligibility: inclusion and exclusion criteria

The inclusion criteria will consider the following:apatients who seek dental treatment at the School of Dentistry;bare aged 18 to 60 years;cpatients who present at least one restoration of composite resin or amalgam on a permanent posterior tooth.

The exclusion criteria will consider the following:apatients who refuse to participate in the research;bpatients who present systemic conditions or chronic diseases that require differentiated care and follow-up. These cases will be referred to the specific services available at the School of Dentistry.crestorations on teeth with conditions as fistula, abscess, pulp exposure, history of spontaneous dental pain, or mobility will not be included.

#### Interventions

Firstly, all patients’ dental surfaces will be examined according to the International Caries Detection and Assessment System (ICDAS) [13]. Patients meeting the inclusion criteria will be classified into subgroups. The individuals will be classified according to caries experience using the Decayed, Missing, Filled permanent Teeth (DMF-T) in 2 groups: index less or equal to 4, or index greater than 4; and also, according to the caries activity (with or without caries activity), for later block stratification.

In this first appointment, a questionnaire will be applied to assess the impact of oral health on adults’ quality of life. The instrument used will be the validated Brazilian version of the Oral Health Impact Profile-14 (OHIP-14) questionnaire [15].

The participants will be allocated into two groups (Fig. 1) according to the strategy used to diagnose and determine the treatment for caries lesions around restorations.a*FDI group* Diagnosis and treatment decision based on the International Dental Federation (FDI) criteria (Fig. 2).b*Experimental group* Diagnosis and treatment decision according to Caries Associated with Restorations or Sealants (CARS) detection criteria, described in the ICCMS (Figs. 3, 4).

**Fig. 1 Fig1:**
[figure not shown]
Study process

**Fig. 2 Fig2:**
[figure not shown]
International Dental Federation (FDI) criterion linked to the treatment decision [12]

**Fig. 3 Fig3:**
[figure not shown]
Caries-Associated with Restorations and Sealants (CARS) Detection Criteria [13]

**Fig. 4 Fig4:**
[figure not shown]
Treatment decision linked to Caries Around Restorations System—CARS adapted

A calibrated examiner will perform a clinical examination of the restorations. The calibration was conducted in two phases. In phase I, a series of photos on restorations with marginal defects were projected in a television in a dark room for the examiner and one expert in restorative dentistry with training and experience in the diagnosis of restorations (gold standard). The discussion of the cases was performed. Phase II was completed at the clinic; both examiner and gold standard examined a total of 20 patients, attributing the diagnosis and treatment according to FDI and CARS for each case. The answers were compared in the end, and disagreements were discussed.

In the clinical trial, after the clinical examination, the calibrated examiner will establish the treatment plan, according to the treatment indications of the criteria in which the patients were allocated. The same examiner will re-evaluate the restorations according to the other criteria. However, this procedure will only serve to future comparison among the methods. This new re-evaluation will not influence the classification and treatment proposed by the first criterion used.

The tests will be conducted in a dental chair under lighting after the teeth are cleaned with a low-rotation micromotor, rubber cup, and Robinson brush using prophylactic paste. The exams will be performed with a dental mirror and a ballpoint probe. To assess the restorations of patients allocated in the FDI group, all surfaces will be dried before evaluation [12]. For the assessment of the experimental group’s surfaces, the teeth will be evaluated wet and then dry for 5 s using the triple syringe, according to the protocol established by the ICCMS [13].

#### Dental treatment protocols

The restorations, therefore, will be submitted to the proposed treatment according to the first evaluation performed. These treatments will be performed according to predefined protocols by operators blinded to the criterion used to reach the treatment decision.

In all situations, the carious tissue, if present, will be removed, as well as the dental restorations, when indicated.

Both repair and replacement of restorations will be performed following the adhesive protocol described by the manufacturer (Adper Scotchbond Multi-Purpose, 3M ESPE, USA) to the use of resin restorations. The conventional composite resin (Filtek Z350 XT, 3M ESPE, USA) will be inserted on the cavity using increments. Besides the proposed treatment for restorations, other necessary treatments for the patient will also be performed. Additional treatments (not involving repairs/replacements) will be planned/defined by the operator responsible for the patient's initial clinical examination.

#### Follow-up visits

After completing the treatment performed at the last restoration of each participant, they will return to evaluate the outcomes after 6, 12, 18, 24, and 60 months.

The restorations will be evaluated through clinical inspection (mirror and ballpoint probe) by a previously calibrated examiner. The treatment needs will be established according to the demands of the patients. The examiner will be blind concerning previous allocation groups and previously performed treatments. If the patient needs further treatment-related or not to restorations, it will be performed.

The instrument OHIP-14 will be reapplied 1 week after the patients receive all the interventions needed, at 24 months and 60 months, to assess the impact on the long-term quality of life.

#### Outcomes

The primary outcome will be restoration failure. The secondary outcomes will be the differences obtained comparing the two indices in relation to the treatment decision, the number of false-positive results (cases initially indicated to repair or replacement, in which during the intervention no decayed tissue was found), the impact of the intervention on quality of life and cost-effectiveness.

### Participant timeline

The study will be recruiting patients from October 2016 to February 2020. The study’s enrollment for each participant will lead approximately 61 months, estimating 1 month of treatment and 60 months of follow-up. The study phases are presented in Fig. 5.

**Fig. 5 Fig5:**
[figure not shown]
Standard protocol items: enrolment, interventions, and assessments

### Sample size

The sample calculation was performed based on the primary outcome of the randomized clinical trial (percentage of restorations requiring reintervention). The calculation considered a 2-year failure rate of approximately 10% for occlusal restorations [16] and 30% for occlusal-proximal restorations [17]. It was also assumed that about 10% of the replaced restorations and 14% of the restorations undergoing repair fail again [18]. Thus, estimating that half of the sample is from occlusal restorations, an operative reintervention requirement rate of 24% was estimated in 2 years. The number of 522 restorations was reached, based on an absolute difference of 10% between the groups, using a two-tailed test. As a participant can contribute with more than one restoration, 20% was added to this value (n = 626). Thus, considering a predetermined average of inclusion of 5 teeth per patient, and adding 20% to possible sample losses, a minimum number of 152 patients was reached to be included in the trial.

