### Data collection, management, and analysis

The follow-up assessments will be performed by a pre-calibrated examiner, who does not have previous contact with the patient and with last information about the allocation groups and treatments performed. The treatment needs will be established according to the demands of the patients.

The clinical data will be registered on sheets previously organized on Microsoft Excel Software. All data, except those that might reveal the participants’ identities, will be shared in a public repository after accepting all manuscripts related to these studies.

The survival analysis will be used to analyze the primary outcome. Kaplan–Meyer graphs will be constructed, and the methods will be compared to each other with Cox regression with shared frailty. The calculation of sensitivity, specificity, and accuracy will consider the results obtained with the indices and the classification of the presence or not of caries lesion by the proposed reference standard. 95% CI values will be calculated with adjustments as one individual may have more than one restoration included, using a suggestion previously published [19]. The sensitivity, specificity, and accuracy between the methods will be compared using multilevel analysis (3 levels: assessment, tooth, and child/adults). As also, for the comparisons between the treatment decisions obtained with the different criteria. The cost-effectiveness ratio will also be verified, considering as effect the prevention of the primary outcome, as well as other secondary endpoints of interest, and the cost spent to reach such a condition with each of the indices. For all tests, two-tailed analyzes will be used, considering a level of significance of 5%. Analyzes will be performed using the statistical package Stata 15.0 (Stata Corp, College Station, USA).

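### The primary Cox comparison names no adjustment for restoration type, although the sample-size inputs make type strongly prognostic; prespecifying it would recover a modest amount of power at little cost

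*Protocol article*

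**What the plan says.** All references are to the protocol article.

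- **Sample size.** Two-year failure is set by type: "The calculation considered a 2-year failure rate of approximately 10% for occlusal restorations [16] and 30% for occlusal-proximal restorations". The types are then pooled: "estimating that half of the sample is from occlusal restorations, an operative reintervention requirement rate of 24% was estimated in 2 years". The size follows from the pooled rate: "The number of 522 restorations was reached, based on an absolute difference of 10% between the groups, using a two-tailed test".
- **Allocation.** Patients are randomised in four strata, formed by DMF-T (up to 4, above 4) and caries activity (present, absent). Restoration type is not a stratum.
- **Data collection, management, and analysis.** For the primary outcome, "the methods will be compared to each other with Cox regression with shared frailty". No covariate is named. The section does not say that the model is unadjusted.
- **Interventions.** Before allocation, "all patients’ dental surfaces will be examined according to the International Caries Detection and Assessment System".

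**The concern.** The planning treats restoration type as a main driver of failure, and the stated primary comparison then makes no use of it. Type is a feature of each restoration and exists before allocation. Patients are randomised with about five restorations each, so the mix of types in each arm is left to chance.

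A Cox model without a strong prognostic factor has three known consequences. The treatment hazard ratio is somewhat closer to 1 than the ratio within types. Chance differences in mix are not corrected. Precision is lower than it could be. The shared frailty term does not remove this, because it acts on the patient and type can vary among one patient's teeth. What is at stake is efficiency and how the hazard ratio is read. The validity of the trial is not in question.

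**Working it through.** **1. The plan's own figure.** Inputs are 24% versus 14%, two-sided alpha 5% and 1:1 allocation. Power is not stated, so 80% is assumed. With continuity correction this gives 261 per arm, or 522, which matches exactly. Then 522 × 1.2 = 626; 626/5 = 125.2, so 126 patients; 126 × 1.2 = 151.2, so 152. The 522 therefore compares pooled rates, with the mix of types already averaged in. Without continuity correction, 261 per arm gives 83% power for that comparison.

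**2. Strength of type.** With constant hazards, HR = ln(1 − 0.30)/ln(1 − 0.10) = 0.3567/0.1054 = 3.39.

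**3. Chance imbalance.** Retained patients: 152 × 0.8/2 ≈ 61 per arm, or 61 × 5 = 305 restorations. With half of each type, the SD of the between-arm difference in occlusal-proximal share is √[2 × 0.25 × (1 + 4 × ICC)/305]. The ICC of type within patients is not in the document and is assumed. The effect on failure is 1.96 × SD × 0.20, where 0.20 is the gap between 30% and 10%.

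| ICC of type | SD of difference | 95% range | Effect on failure |
|---|---|---|---|
| 0.1 | 0.048 | ±9.4 points | ±1.9 points |
| 0.2 | 0.054 | ±10.6 points | ±2.1 points |

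That is about a fifth of the 10-point target at the extreme. One SD is worth about 1 point of failure.

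**4. Hazard ratio with and without type.** Exponential hazards, a 50:50 mix and a type HR of 3.39 are scaled so that the pooled two-year rate is 24%. The treatment HR within type is then the one that gives 14% (or 34%) pooled. The value without type is the large-sample limit of the Cox estimate. The loss is 1 − ln(HR without type)/ln(HR within type).

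| Comparison | HR within type | Without, 2 years | Loss of log HR | Without, 5 years | Loss of log HR |
|---|---|---|---|---|---|
| 24% vs 14% | 0.539 | 0.549 | 3.1% | 0.564 | 7.5% |
| 24% vs 34% | 1.551 | 1.516 | 5.2% | 1.473 | 11.8% |

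Both directions are shown because the test is two-tailed.

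**5. Power with and without type.** Simulation: 2,000 runs, 126 patients with 5 restorations each, Cox regression with cluster-robust standard errors. Frailty variance is assumed.

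| Scenario | 14% case, with / without | Gain | 34% case, with / without | Gain |
|---|---|---|---|---|
| No clustering | 91.4 / 90.0 | 1.4 | 83.6 / 78.6 | 5.0 |
| Type ICC 0.2 | 92.3 / 87.7 | 4.6 | 84.9 / 77.7 | 7.2 |
| Type ICC 0.2, frailty variance 0.5 | 73.9 / 71.8 | 2.1 | 56.9 / 53.2 | 3.7 |

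With no treatment effect, rejection was about 5 to 6.5% with or without type.

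A second simulation agrees (2,500 runs, true HR 0.55, strata in both models, frailty variance 0.2, assumed HR 2 for caries activity and 1.5 for DMF-T). At 24 months the HR was 0.546 with type and 0.558 without, with power 82% and 78%. At 60 months it was 0.549 and 0.569, with power 96% and 93%.

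**The case against.** The strongest reply is that the absence of type is read from silence. The article is condensed, covariate lists often sit in an analysis plan that is not shown, and nothing in the text excludes type. This stands as a limit: a reader might infer that the plan rejects adjustment, and it does not say so. The point is that the primary comparison as published makes no use of a factor on which the same document leans heavily.

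Several stronger readings are tempting and fail.

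- **That 522 is too small because of type.** It was set on the pooled 24% rate, so the mix is already in it.
- **That the hazard ratio without type is biased.** Under randomisation, imbalance in type is chance error, and the simulated type I error is unchanged. The value nearer 1 reflects non-collapsibility: it is a different, marginal quantity.
- **That type should have been a stratum.** Patients are randomised and type varies among their restorations, so it cannot be a simple stratum.
- **That type is the strongest predictor known.** The document gives no effect sizes for caries activity or DMF-T. The 10% and 30% are approximate planning values from two different cited sources, so 3.4 is a ratio across sources plus an assumption of constant hazards.

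It is also fair to object that the article does not say that the baseline surface examination records the extent of each restoration. That bears on the cost of the fix and is taken up there.

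**Conclusion.** The point holds as a modest gain in efficiency left unused. On the plan's own inputs, adjusting for type raised power in every scenario simulated, by about 1 to 7 points. It would correct a chance imbalance worth about 2 points of failure at the 95% extreme. It would also give a hazard ratio that does not drift toward 1 over follow-up because of type: about 3 to 5% of the log hazard ratio at 2 years and 8 to 12% at 5 years.

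These sizes rest on 80% power, constant hazards, a half-and-half mix, a type ICC of 0 to 0.2 (0.1 to 0.2 for the imbalance figure) and a frailty variance of 0 to 0.5. The main power simulation used cluster-robust Cox regression. The planned shared frailty may absorb some of the between-patient variation in type, so the gain under the planned model could differ somewhat.

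**What to change.** Prespecify restoration type, occlusal only versus involving a proximal surface, as a restoration-level covariate in the primary Cox shared-frailty model. Define it by the restoration's extent before any trial treatment. Extent recorded after repair or replacement could depend on the allocated criterion and should not be used. Report the model without type as a sensitivity analysis. If a fuller analysis plan already lists type in this form, nothing more is needed.

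The cost is one covariate and no change to visits or sample. There are two small downsides. The hazard ratio becomes conditional on type and should be described that way. Pre-treatment extent must also be available: if the baseline surface examination did not record it, it has to be coded from the restoration as it stood before treatment, preferably by someone unaware of allocation.

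### The 20% loss allowance is applied as a multiplication, so 152 patients leave 608 restorations rather than the planned 626; the 20% for clustering corresponds to ICC 0.05 with equal numbers and leaves no margin

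*Protocol article*

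**What the plan says.** The section on sample size in the protocol article prints its chain of figures. It takes a two-year rate ("an operative reintervention requirement rate of 24% was estimated in 2 years") and sizes the trial "based on an absolute difference of 10% between the groups, using a two-tailed test". From this, "The number of 522 restorations was reached". The first inflation is for clustering: "As a participant can contribute with more than one restoration, 20% was added to this value", giving 626. The total is then divided by an average of 5 teeth per patient and inflated a second time: "adding 20% to possible sample losses, a minimum number of 152 patients was reached to be included in the trial".

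The section gives no power, no intraclass correlation (ICC) and no spread of restorations per patient. The eligibility section admits patients who "present at least one restoration of composite resin or amalgam on a permanent posterior tooth". Patients, not restorations, are randomised, and the primary analysis is a Cox model with shared frailty.

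**The concern.** There are two separate issues.

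- **Loss.** To keep a required number after losing a fraction d, one divides by 1 − d. Multiplying by 1 + d gives a smaller number. If the second 20% is a loss rate, the stated minimum does not deliver the restorations that the same paragraph says are needed.
- **Clustering.** With patients randomised and restorations counted, the clustering multiplier is a design effect. It depends on the ICC and on how the number of restorations varies between patients. A flat 20% fixes both without naming either. If the true design effect is larger, the 626 restorations are worth fewer than 522 independent ones.

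At stake is whether 152 patients carry the power that 522 independent restorations were meant to give.

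**Working it through.** **Inputs from the protocol article:** 24% two-year rate; 10-point absolute difference; two-sided 5%; 522, 626 and 152; average of 5 per patient; 20% for clustering; 20% for losses.

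**Assumed because not stated:** 80% power, 1:1 allocation, and 24% versus 14% as the direction of the difference. Together, with a continuity correction, they reproduce 522. The ICC and the coefficient of variation (CV) of restorations per patient are also assumptions and are shown as ranges.

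**1. Reproducing the plan**

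- Two proportions, 0.24 versus 0.14, pooled variance under the null, continuity-corrected: 261 per arm, 522 in total. Other variants miss: 482 without the correction, 684 for 24% versus 34% with it, and 684 for 90% power with it.
- 522 × 1.2 = 626.4, taken as 626.
- 626 / 5 = 125.2, taken as 126.
- 126 × 1.2 = 151.2, taken as 152. Without the intermediate rounding, 125.2 × 1.2 = 150.24, or 75.12 per arm; rounding each arm up to 76 also gives 152. Either way the factor is 1.2.

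**2. Loss step**

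- Remaining after 20% loss: 152 × 0.8 = 121.6 patients; 121.6 × 5 = 608 restorations.
- Shortfall: 626 − 608 = 18; 18 / 626 = 2.9%.
- Division instead: 125.2 / 0.8 = 156.5, so 157 patients, or 158 for equal arms.
- Loss that 152 patients tolerate: 1 − 626 / (152 × 5) = 1 − 626 / 760 = 17.6%.
- Power at the plan's own design effect: 608 / 1.2 = 507 effective restorations instead of 522. Power goes from 80.2% to 78.9% with the continuity correction, and from 83.1% to 82.0% without it.

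**3. What the clustering 20% implies**

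- Equal numbers: 1 + (5 − 1) × ICC = 1.20, so ICC = 0.20 / 4 = 0.05.
- Unequal numbers: design effect = 1 + ((1 + CV²) × 5 − 1) × ICC. At ICC 0.05, any CV above zero pushes it past 1.20.
- Numbers will vary. Five is an average, one restoration is enough to enter, and two of the four randomisation strata have a DMF-T of 4 or less, an index that counts teeth. Those patients cannot have 5 restored teeth.

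**4. Power with the 608 restorations left after 20% loss**

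| Assumed ICC | Design effect, CV 0 to 0.8 | Effective restorations | Power, corrected | Power, uncorrected |
|---|---|---|---|---|
| 0.02 | 1.08 to 1.144 | 563 to 531 | 83% to 81% | 86% to 84% |
| 0.05 | 1.20 to 1.36 | 507 to 447 | 79% to 73% | 82% to 77% |
| 0.10 | 1.40 to 1.72 | 434 to 353 | 72% to 62% | 76% to 67% |

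**5. Break-even.** The 608 restorations are worth 522 when the design effect is 608 / 522 = 1.165. With equal numbers this is ICC = 0.165 / 4 = 0.041. With CV 0.8 it is ICC = 0.165 / 7.2 = 0.023, where 7.2 = 1.64 × 5 − 1.

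**The case against.** Five points can be made for the plan.

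- **Adding 20% may mean exactly that.** Read literally, multiplying by 1.2 contains no slip. But the addition is made for losses, and the loss it covers is then 17.6%, which the text does not say.
- **Lost patients are not wholly lost.** The primary analysis is survival-based, with visits at 6, 12, 18, 24 and 60 months. A patient who leaves after a visit contributes until censoring, and follow-up to 60 months may yield more events than the two-year proportion used for sizing. This stands. The figure of 608 is the count with complete follow-up, and the power cost of about one point is an upper bound in that sense.
- **The continuity correction is not part of a Cox analysis.** Also true. It is used here because it reproduces 522; without it, power is about 2.5 to 5 points higher.
- **The ICC of 0.05 is inferred.** The authors never state it, so it should be called what the 20% corresponds to, not what they assumed.
- **An article may leave the ICC to the full protocol.** Fair, so its absence alone is not the point. The point is that the printed multiplier has a definite meaning and no room to spare.

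A reader might infer that both allowances fall short and that the trial is underpowered. The documents do not support that for the clustering step. They give no ICC and no spread of numbers per patient, and at an assumed ICC of 0.02 even CV 0.8 requires only 522 × 1.144 / 5 / 0.8 = 149.3, or 150 patients.

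**Conclusion.** The loss step is wrong on the plan's own figures if the 20% is a loss rate: 608 restorations remain where 626 are called for, and the stated minimum is 5 to 6 patients too low. The consequence is minor.

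The clustering step is conditional. Its 20% is enough for ICC 0.05 only if every patient has exactly 5 restorations, which the eligibility rule, the word average and the DMF-T strata rule out. After 20% loss, the size is adequate below an ICC of about 0.02 to 0.04, depending on the spread, and inadequate above it. At ICC 0.10 the power loss would be much larger than anything the loss step causes.

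The power figures rest on 24% versus 14%, 1:1 allocation and 80% power, and on the ICC and CV values, none of which the protocol states.

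**What to change.** In the sample-size section:

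1. Either give the patient number by division by 0.8 (157, or 158 for equal arms), or keep 152 and state that it tolerates 17.6% loss.
2. State the power, and that the 20% for several restorations per patient corresponds to ICC 0.05 with 5 in every patient.
3. Report the power of 152 patients over an ICC range of about 0.02 to 0.10, using 1 + ((1 + CV²) × 5 − 1) × ICC with a stated CV. The CV among patients already enrolled would serve and needs no outcome data.

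The cost is a few sentences and a slightly less favourable stated power or tolerated loss. Restating the figures is enough; no added enrolment and no change to design or analysis is required.
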